**Figure 2: Study Timeline**

**2.16 Data Analyses:**The assumptions for parametric analyses will be evaluated. Normal distribution will be evaluated using the one-sample Kolmogorov-Smirnov test. Qualitative comparison of variable balance will be made, including determination of prognostic importance. Descriptive statistics of training time and number of training sessions for the treatment group (collected via tablet usage data) will be used to evaluate dose-response and adherence.

***Clinical Outcomes:*** Analyses will be conducted on a per-protocol basis (i.e., participants who completed the study) and then on an intention-to-treat basis for comparison (i.e., using multiple imputation).79 All primary and secondary outcomes will be compared between the intervention and control groups, using analysis of covariance (ANCOVA), controlling for baseline score and inpatient and outpatient units. To explore the findings, ANCOVA will be used to compare secondary clinical outcomes between groups. Endpoint and change score analysis of variance (ANOVA) tests will also be conducted to compare precision with ANCOVA for sensitivity analyses. To glean a better understanding, we will disaggregate the data by sex/gender and *key outcomes* (e.g., walking capacity and physical activity identity) and explore differences in our study.

***Study and intervention fidelity, and participant experience:***All audio-recordings of the qualitative interviews at T3 will be transcribed verbatim. Thematic data analyses80 will be used to identify key themes in the qualitative interviews. Three methods will be used to promote trustworthiness. Field notes will be used as a self-reflexive tool and member checking, (i.e., key participants will be invited to review the findings to determine how well they resonate with them). Multiple investigators will be involved in data coding as a form of triangulation. Interview results will complement the quantitative results to provide a more in-depth assessment of benefits and user acceptability.59

**2.17 Frequency of analyses:**An interim data analyses will be performed on the primary outcome when 50% of participants have completed T2. An independent blinded statistician will conduct the analyses and report findings to the Data and Safety Monitoring Committee (see *section 3.3*). If the results indicate the SMART or control arm is superior and sufficient information is available, we will terminate the trial to reduce subject burden.

**2.18 Sub-group analyses:**We will do a sub-group analysis to assess the differences in outcomes regards to sex, gender and amputation cause (Diabetes and dysvasuclar vs. others).

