# 2. the proposed trial

**2.1 Study Design:**This is a Type 1 Effectiveness-Implementation Hybrid Design2 1:1 parallel single (assessor)-blinded randomized controlled trial (RCT) conducted online with participants from four Canadian sites (B.C.; London, ON; and two in Toronto, ON) to evaluate the 6-week effectiveness (and the 4-week retention effect) of SMART on patient-relevant outcomes, while documenting implementation factors.59Following the [RE-AIM](http://www.re-aim.org/) framework, a planning tool for implementation evaluation,60 we will assess the implementation of SMART. Also, a small end-of-trial qualitative study will be used to understand participants’ experience.61

**2.2 Trial Interventions:** Participants allocated to the intervention group will receive usual care after the LLA and access to **SMART**. We provide a detailed description of SMART using the TIDieR (Template for Intervention description and Replication) checklist62 provided in **Appendix B**. In **Appendix C** we provide a list of BCTs adopted for each module according to our systematic review and meta-analysis.41 Participants will access the SMART platform using their own computer/tablet, and will be screened for having a computer/tablet before enrolling in the study. In rare cases where a participant in B.C. does have a tablet, they may receive a tablet (Apple’s iPad) preloaded with a dedicated icon to enable direct connection with the SMART platform, if needed. Tablets will not be able to be provided to participants in Ontario.

**Content:** SMART is web-based eHealth intervention that has six educational and skill development modules. SMART is accessible through this link: <https://360.articulate.com/review/content/1afbca12-f6bb-465e-b40f-1029a6fa981b/review>

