**2.4 Protecting against bias - Blinding:**Blinding of participants for the RCTs on the effect of eHealth interventions is impossible because of nature of intervetnions.66 Therefore, it is difficult to blind participants to the intervention received. The assessors will be blinded to group allocation, we will complete the primary outcome (TUG and ASCQ) first, and participants will be asked not to disclose their group allocation during assessments.66 Furthermore, we will have separate trainers for each group (to minimize trainer bias); and the primary outcome measure, the TUG is a performance-based measure with standardized instructions. Finally, all statistical analyses will be conducted by a blinded statistician.

**2.5 Inclusion and Exclusion Criteria:**To be included, participants will: have a unilateral dysvascular- or diabetic- related LLA (transtibial or transfemoral);3have conducted the casting for their initial prosthetic limb (up to 2 years); be aged ≥ 50 years (85% of adults with LLA);3 have a computer or tablet and have access to the internet, and self-identify as being able to speak and read English. We will exclude adults with substantial health conditions (e.g., congestive heart failure, diagnosed dementia); those anticipating further surgery (e.g. LLA revision) as identified by our study sites’ physiatrists; and an ability to use a tablet (e.g./ using hands for typing). Given these criteria, the results of this study will not be generalizable to all adults with LLA such as the very young and those who do not speak English. As most people with LLA are >50 years old and more than 90% of the population of BC and ON speak English, we are confident of obtaining a representative sample.

**2.6 Duration of Intervention:**Participants in the SMART group will receive the intervention for six weeks. Participants in the control group will be contacted weekly for a similar 6 week period.

**2.7** **Frequency and Duration of Follow-up:**There are six weekly SMART modules with each taking approximately 20 to 30 minutes to complete. Individuals will be encouraged to complete one module a week to reduce any perceived burden, and gradually integrate the information. Participants from both groups will receive a weekly contact: SMART group participants will receive a 20 minute telephone call/Zoom video call from peers, and the Control group participants one email or phone call by trainer.

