**2.10 Sample Size:**Our sample size calculation is based on identifying SMART is more effective than standard care from a clinical point of view (Clinical Superiority design),75 and minimize any potential waste of resources.76 We are planning to compare the 2-MWT using a ratio 1:1. In a previous study, the mean (SD) of clinically important change in distance walked in 2 minutes at discharge from the rehab facility was 13.6 (19.9) m in adults with unilateral LLA (mean age = 66 y).37 Assuming minimum important difference of 13.6 m, we will need to enroll a minimum 34 participants per group to be enable to reject a null hypothesis of no difference in means of walking capacity between the 2 groups with 80% power. The type-I error probability associated with this 2-sided test of the null hypothesis is 0.05. Our sample size is based on the feasibility of recruiting 2 adults aged over 50 years with an LLA, per site within 18 months, and with 68 participants at final assessment (accounting for participant attrition) we can have enough power to detect a difference in the primary outcome, i.e., 2-MWT. Acknowledging the challenges with participants,77 20% attrition rate, and non-compliance rate in RCTs, we will recruit 82 participants (41 per arm including both men and women).The target sample size will also facilitate estimates for adherence, and the number of participants with certain covariates (e.g., sex, gender), and inform the sample size calculation and stratification for the implementation study.

**2.11 Health services research issues:** Cost and cost-effectiveness of eHealth interventions have been demonstrated for patients with chronic disease conditions.78 However, we will not do a formal cost analysis in this study.

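### The analysis named first covers only people who completed the study, with intention-to-treat kept for comparison; this exposes the leading result of a superiority effectiveness trial to selection bias

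*Protocol*

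**What the plan says.** Section 2.16, under clinical outcomes, sets the order of the analysis populations: "Analyses will be conducted on a per-protocol basis (i.e., participants who completed the study) and then on an intention-to-treat basis for comparison". The intention-to-treat analysis is to handle missing data ("i.e., using multiple imputation"). Primary and secondary outcomes are compared by ANCOVA adjusting for baseline score and inpatient or outpatient unit. No other section puts intention-to-treat first.

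Section 2.1 describes a "Type 1 Effectiveness-Implementation Hybrid Design" and a "1:1 parallel single (assessor)-blinded randomized controlled trial (RCT". Section 2.10 bases the sample size on "identifying SMART is more effective than standard care from a clinical point of view (Clinical Superiority design"), allows for 20% attrition as well as non-compliance, and recruits 82 people, 41 per arm. Section 2.9 sets T2 within one week of the end of the intervention and T3 four weeks after the intervention. Section 2.17 plans an interim analysis of the primary outcome once half the participants have completed T2; its result can end the trial.

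**The concern.** The effect of offering SMART is a question about everyone randomised. Completers are selected after randomisation, so comparing them is protected by randomisation only if leaving is unrelated to outcome or works alike in both arms.

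The protocol gives reasons not to take that for granted. Under section 2.7 the SMART arm is asked for six modules and a weekly 20-minute peer call, the control arm for one weekly email or call. Section 2.4 concedes that "it is difficult to blind participants to the intervention received". Section 1.5 names over-exertion, residual-limb skin breakdown and low mood after missed goals as possible harms; any of these could lead both to withdrawal and to a worse result.

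The set is also mislabelled. Completing the study says nothing about adherence. It keeps a person who attended every assessment but opened no module. Read literally, it drops a person whose 6-week outcome was observed at T2 but who missed T3. It does not fit the interim analysis either, because some people with T2 data cannot yet have completed the study at that point.

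If the two analyses disagree, the present wording lets the non-randomised comparison lead.

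**Working it through.** **1. The protocol's own figures (section 2.10).** Difference 13.6 m, SD 19.9 m, two-sided alpha 0.05, power 80%:

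n per arm = 2 × (1.960 + 0.842)² × (19.9/13.6)² = 2 × 7.849 × 2.141 = 33.6, so 34. This reproduces the stated 34 per arm (68 in total). The 82 recruited equals 68 × 1.2 = 81.6, rounded up.

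**2. How many people the first-named analysis leaves out.** At the planned 20% attrition, 82 × 0.20 = 16.4, so about 16 are omitted and about 66 analysed (82 × 0.80 = 65.6).

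**3. When the omission matters.** Let p be the share dropping out of an arm (S for SMART, C for control) and g the number of SDs by which dropouts do worse than completers in that arm. The unadjusted completer contrast differs from the all-randomised contrast by (pS × gS − pC × gC) SD.
- If g = 0 in both arms, the bias is 0.
- If pS = pC = 0.20 and gS = gC, the bias is 0.
- Otherwise its sign and size depend on p and g by arm, which the protocol does not give.

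**4. Illustration for the planned ANCOVA.** Every input in this step is assumed: no true effect; dropout 30% in SMART and 10% in control; correlation ρ between outcome and propensity to stay of 0.3 to 0.5; baseline-outcome correlation r of 0.5 to 0.8.

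Under a bivariate normal model, completers' mean outcome shifts by ρ × φ(z)/(1 − p), with z the normal quantile at p. The multiplier φ(z)/(1 − p) is 0.497 at p = 0.30 and 0.195 at p = 0.10, a difference of 0.302.
- Unadjusted contrast: 0.302 × 0.3 = 0.09 SD; 0.302 × 0.5 = 0.15 SD.
- Baseline-adjusted contrast, if dropout acts through the outcome itself: approximately ρ × (1 − r²) × 0.302. Lowest: 0.3 × (1 − 0.64) × 0.302 = 0.033 SD. Highest: 0.5 × (1 − 0.25) × 0.302 = 0.113 SD.

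Simulating the same model gives slightly larger values, because selection flattens the slope on baseline a little; about 0.03 to 0.12 SD covers them.

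The mechanism matters. If dropout acts only through baseline, the completer ANCOVA bias is about 0. If it is unrelated to baseline, adjustment removes none of the unadjusted bias.

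**5. What imputation adds.** In simulations where dropout depends on the outcome, imputing by arm from baseline alone left practically the same bias as the completer ANCOVA (for example 0.068 against 0.068 SD, and 0.079 against 0.082 SD). A gain needs information the completer ANCOVA lacks, chiefly T2 scores from people who miss T3.

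**The case against.** The protocol never calls the completer analysis primary. Both analyses are prespecified, with a missing-data method, and a statistical analysis plan not shown here might rank them differently. This stands to a degree: the defect is one of ranking and labelling, not of a missing analysis. But the order and the comparison role given to intention-to-treat are set in the protocol, and a later plan that follows it would inherit them.

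The protocol also works to limit loss: coordinator contact every 4 weeks and $25 per assessment in both arms (sections 2.14 and 2.12), weekly contact in both arms (section 2.7), and trainer contact after 7 days of inactivity on the platform (section 2.2). Section 2.14 cites under 20% loss in a prior study. Nothing in the protocol points to 30% versus 10%. This stands, and is why those rates are an illustration only.

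A reader might infer that the leading result will be biased towards SMART, by 0.09 to 0.15 SD or 13% to 22% of the planned 0.68 SD effect, with type I error of 6.5% to 9.4%. The protocol does not support that:
- Those figures come from an unadjusted comparison under assumed dropout, whereas section 2.16 plans adjustment for baseline.
- The 0.68 SD (13.6/19.9) belongs to another measure. Section 2.10 says "We are planning to compare the 2-MWT using a ratio 1:1", while section 2.8 names the Timed Up and Go as the primary outcome.
- Neither the direction nor the size of dropout bias can be read from the text.

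Finally, promoting intention-to-treat with imputation does not cure dropout that depends on unobserved outcomes. That is correct, but it is no reason to lead with completers.

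**Conclusion.** The point holds as one of ranking and definition. A superiority trial of effectiveness that expects 20% attrition should not lead with an analysis omitting about 16 of 82 randomised people, nor call that set per-protocol when it does not measure adherence.

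What is established is exposure to bias, not a known bias. It is zero if dropout is unrelated to outcome, or balanced and equally prognostic. The figure of about 0.03 to 0.12 SD for the completer ANCOVA rests wholly on the assumed dropout rates and correlations, and on dropout acting through the outcome itself. It should not be read as a forecast for this trial.

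**What to change.** In section 2.16:
- Name as primary the intention-to-treat ANCOVA on all randomised participants as allocated, using every observed T2 outcome and the multiple imputation already planned. The imputation model should contain arm, baseline, and T2 and T3 scores. Platform use can enter only if imputation is done within the SMART arm, since controls have no platform data.
- Label the completer analysis supportive and call it a completer analysis.
- If a per-protocol analysis is wanted, define it by modules completed and contacts received.

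In section 2.17, state that the interim analysis uses the same intention-to-treat set.

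The cost is protocol wording, as both analyses are already planned. One limitation remains: the imputation assumes that dropout depends only on observed data.

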**Control Intervention:**Participants in the control arm will receive usual care after LLA, education, and social calls. The education booklet is typically offered to patients at discharge, and includes information about LLA consequences, adjusting to amputation, pain management, limb positioning and exercises, mobility (e.g., wheelchair safety, hopping, and transfers), residual limb management (e.g., skin care and diabetic foot care), tips for preparing the home, and driving. A single weekly structured email or telephone contact (based on preferences, n=6 in total) will be made by the trainer. The purpose of the contact is to answer any questions, and to help control for attention bias.45

**2.3 Allocation - Sequence Generation and Randomization:**We will use a central computerized randomization process with variable block sizes to randomly allocate the participants to the intervention (SMART) group or control group using a 1:1 ratio by an independent statistician.

An independent statistician will provide the randomization list through REDCap (REDCap Software, Vanderbilt University and National Institute of Health, USA). The research coordinator will obtain written informed consent (Over Qualtrics platform) and a blinded assessor will complete the baseline assessment. The research coordinator will meet with the participant over Zoom (a secure, UBC-based platform) to guide them through the consent form and answer any questions. At the completion of baseline assessment, the research coordinator will log onto the system to determine the next allocation. The research coordinator will work with the group trainers to set up an appointment. Our protocol for all participants is to complete the baseline assessment, randomization and training within two weeks.

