***Implementation:*** Following the [RE-AIM](http://www.re-aim.org/) framework,60 five elements of implementation will be assessed including, reach (target population), effectiveness (effects of SMART), adoption (by setting/staff), implementation (dose delivered and received, fidelity to the intervention), and maintenance of the behavior (in target population and settings). During study, the research coordinator will keep the detailed logs to monitor fidelity to research protocols and review the online chart for the adherence to the SMART (dose). Moreover, ***participant experience*** will be identifiedwith a brief30-minute audio-recorded semi-structured in-person interview with men and women (n=20) from the experimental group (*Section 2.2*) by the researcher at the end of the study (T3) to explore the experience and acceptability of the SMART program, health related goals, and any perceived disadvantageous of SMART. Moreover, we will call any dropout participants to obtain their feedback.

***Sociodemographic and Clinical Characteristics***: We will collect descriptive characteristics at T1 (**Appendix E**) including, age, sex, gender, level of education, marital status, weight, height, and clinical variables, such as presence of comorbidities, level, cause, side, and date of amputation, discharge date, date in which prosthetic training has been started, and date in which patient received the permanent prosthesis. We will also collect the participants’ self-report encounters with outpatient rehab care providers (e.g., PT, OT) and surgical consultations throughout the six-week intervention.

A cognitive screen, the Montreal Cognitive Assessment (MoCA) will be used to screen for cognitive impairments.

**2.9 Measuring outcomes at follow-up:** We will collectdata for intervention and control groups at three time points (**Appendix E**): T1=baseline; T2=within one week of completing SMART intervention; T3=retention period of four weeks post-intervention. The one-on-one semi-structured interviews with the SMART group to determine impressions of the protocol and intervention will be conducted at T3. All data collection will occur through online survey link on Qualtrics platform hosted by University of British Columbia. All sessions will be performed on Zoom video call.

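### The ANCOVA adjusts every outcome for an inpatient/outpatient unit variable that the protocol does not define, while usable prognostic variables listed at T1 are left out of the model

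*Protocol*

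**What the plan says.** - **Model.** Section 2.16 (Clinical Outcomes) prescribes one ANCOVA for all primary and secondary outcomes, "controlling for baseline score and inpatient and outpatient units". It names no other covariate.
- **Allocation.** Section 2.3 describes a "central computerized randomization process with variable block sizes" at 1:1 and names no stratification factor.
- **T1 data.** The characteristics listed in section 2.8 include "level, cause, side, and date of amputation, discharge date, date in which prosthetic training has been started", besides demographic items and comorbidities. When the permanent prosthesis was supplied is listed too. No inpatient/outpatient unit appears.
- **Data during the intervention.** Section 2.8 also collects self-reported "encounters with outpatient rehab care providers (e.g., PT, OT) and surgical consultations throughout the six-week intervention".
- **Eligibility.** Under section 2.5, participants "have a unilateral dysvascular- or diabetic- related LLA (transtibial or transfemoral"; casting for the first prosthesis must have been done, with a limit of up to 2 years.
- **Other prognostic variables.** Section 2.16 adds: "Qualitative comparison of variable balance will be made, including determination of prognostic importance". It does not say what follows from that comparison.

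**The concern.** An ANCOVA is prespecified only if each covariate can be coded without further choice. Here one of the two cannot. A statistician could take the unit covariate as the type of unit that recruited the participant, as care status on the day of T1, or as whether inpatient rehabilitation was ever received. These give different models. Unless the term is settled beforehand, the choice falls after data exist, and it affects every between-group comparison.

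There is also a specific trap. The only outpatient item listed is the count of care contacts over the six weeks. SMART might change how often people seek care, so adjusting for that count could remove part of the treatment effect or otherwise distort it.

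Meanwhile amputation level and the date prosthetic training began are listed at T1, both can differ between participants under the eligibility criteria, and neither is in the model. With 34 evaluable participants per arm planned and no stratification stated, prognostic covariates fixed in advance are a cheap way to gain precision.

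**Working it through.** **Text check: is the unit covariate identifiable?**

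| Where it could be fixed | What the protocol gives |
| --- | --- |
| 2.16, the model | The name only |
| 2.3, allocation | Variable blocks, 1:1, no stratification factor named |
| 2.8, T1 characteristics | No unit variable; the nearest baseline item is discharge date |
| 2.8, during the intervention | Outpatient and surgical contacts, after randomisation |
| 2.12 and 2.15, recruitment | Amputee clinics, hospitals and a prosthetics partner; no rule for classing a participant |

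No section supplies a definition.

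**Planning figure.** Inputs from section 2.10: difference 13.6 m, SD 19.9 m (two-minute walk test), two-sided alpha 0.05, power 80%.

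n per group = 2 × (1.960 + 0.842)² × (19.9/13.6)² = 33.6, rounded up to 34. The stated 34 reproduces. The normal approximation gives power 0.805 at 34 per group; the t-test gives 0.793. The t-test value is the reference below.

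**What the replacement covariates could bring.** The proposal adds three terms: level, time since the start of training, and a not-yet-started indicator. Let R² be the share they explain of the variance left after the baseline score. No document gives R², so it is an assumption and a range is shown.

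- Residual degrees of freedom: 68 − 6 = 62 (intercept, arm, baseline score, three terms).
- Standard error factor: f = √[(1 − R²)(1 + 3/62)]. The second bracket is an approximate charge for estimating the three terms.
- Standardised difference: d = 13.6/19.9 = 0.683, replaced by d/f in the t-test power at 34 per arm.

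| R² (assumed) | f | Change in standard error | d/f | Power |
| --- | --- | --- | --- | --- |
| Terms not added | 1 | reference | 0.683 | 0.793 |
| 0 | 1.024 | +2.4% | 0.668 | 0.774 |
| 0.05 | 0.998 | −0.2% | 0.685 | 0.795 |
| 0.10 | 0.971 | −2.9% | 0.704 | 0.816 |
| 0.20 | 0.916 | −8.4% | 0.746 | 0.858 |

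Break-even is where (1 − R²)(1 + 3/62) = 1, so R² = 1 − 62/65 = 4.6%.

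**Limits.** The power column is illustrative. Its d comes from the two-minute walk test, whereas section 2.8 names the TUG and the ASCQ as primary, and no TUG standard deviation is given. The reference is also an unadjusted t-test, not the planned ANCOVA with baseline score, because no baseline correlation is given. The standard error column depends only on R² and the degrees of freedom.

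**The case against.** **A covariate need not be a randomisation factor.** This is right, and the proposed replacements are not randomisation factors either. The missing stratification matters only because it removes one place where the term might have been defined.

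**Not listed is not the same as not collected.** This also stands. The T1 list is open-ended, Appendix E is a figure not shown, and discharge date might allow inpatient status to be derived. An SAP, also not shown, could hold the coding. But the protocol itself fixes this term as one of only two covariates and gives no rule for coding it. The point made here is that the term is undefined and unlisted, not that the data are absent.

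**Leaving out level and prosthetic stage is not an error.** Agreed. Randomisation protects against bias, the standard error already allows for chance imbalance, the baseline score may carry part of the same information, and a check of prognostic balance is planned. The replacement covariates are a recommendation for precision and can cost a little if they predict nothing.

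**Stronger readings that the documents do not support:**

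- A reader might infer that transtibial and transfemoral participants, or early and late prosthesis users, improve at very different rates over six weeks, so that baseline score cannot suffice. The protocol gives no rates of change by level or stage, and no distribution of either at entry. Eligibility shows only what may vary.
- A reader might infer that people cast but not yet fitted would be randomised without a usable baseline TUG. Sections 2.3 and 2.12 place allocation after the baseline assessment is complete, and nothing says that people unable to do the test are randomised. No separate requirement is needed.

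**Conclusion.** The point holds for the undefined covariate. Section 2.16 commits every outcome analysis to a variable that the protocol does not define, list at T1, name as a randomisation factor or give a rule for, and the nearest outpatient item in the data is post-randomisation. This should be corrected in the protocol text.

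The suggestion to use amputation level and time since the start of prosthetic training rests on precision alone. Its value depends on an R² that the documents do not give: a standard error about 3% to 8% smaller at an assumed 10% to 20%, no gain near 5%, and about 2 points of power lost at zero. Nothing here shows that the planned comparison would be biased, provided the contacts during the intervention are kept out of the model.

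**What to change.** 1. Remove the unit covariate from section 2.16. If it is wanted, define it as a status recorded before randomisation, state its categories and the rule for assigning them, and add it to the T1 form.
2. State that care contacts during the six weeks are descriptive and will not be used as a covariate.
3. In its place, prespecify amputation level (transtibial or transfemoral) and time from the start of prosthetic training to T1, with an indicator for training not yet started, alongside arm and baseline score. State the form in which time enters.
4. State that the planned check of balance and prognostic importance is descriptive and does not alter the primary model.

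The cost is wording and 3 degrees of freedom. The replacement covariates use items already listed at T1; only keeping the unit variable would add a field to the form. The change should be made before any unblinded comparison, including the interim analysis in section 2.17.

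### Section 2.17 commits to stopping for superiority at a mid-trial look without a boundary, and Section 2.10 sets alpha and sample size as if there were no look

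*Protocol*

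**What the plan says.** **Section 2.17 (Frequency of analyses)** fixes one look and its timing: "An interim data analyses will be performed on the primary outcome when 50% of participants have completed T2". A blinded independent statistician reports the results to the Data and Safety Monitoring Committee, for which the text refers to a Section 3.3. The consequence follows: "If the results indicate the SMART or control arm is superior and sufficient information is available, we will terminate the trial". The rule works in both directions. It gives no p-value, boundary or spending function, and it does not say what makes an arm superior or when information is sufficient.

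**Section 2.10 (Sample Size)** sets the error rates: "The type-I error probability associated with this 2-sided test of the null hypothesis is 0.05", with the aim of rejecting a null hypothesis of "no difference in means of walking capacity between the 2 groups with 80% power". The size is "Assuming minimum important difference of 13.6 m, we will need to enroll a minimum 34 participants per group". The section does not mention the interim look.

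The measure is also unsettled. Section 2.10 sizes the trial on the two-minute walk test ("We are planning to compare the 2-MWT using a ratio 1:1"), and H1 in Section 1.2 names the same test. Section 2.4 names TUG and ASCQ as the primary outcome, and Section 2.8 makes TUG the operational primary measure.

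**The concern.** A look that can end the trial with a claim of superiority is an extra chance to reject a true null hypothesis. Unless some alpha is set aside for it, the overall error exceeds the level used at the final test. Here the stop, its timing, the alpha and the sample size are all written into the protocol, but only the last two agree with each other.

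Two things are at stake. The first is whether the 5% error rate in Section 2.10 can be claimed for the result. The second is whether the decision to end the trial is fixed before anyone sees interim data. With superiority and sufficient information undefined, the threshold could be chosen when the data are on the table. A stop would also leave fewer participants to inform T3 retention, the sex, gender and cause subgroups, and implementation, all of which the protocol plans to study.

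**Working it through.** **Inputs**
- From Section 2.10: difference 13.6 m and SD 19.9 m ("was 13.6 (19.9) m in adults with unilateral LLA (mean age = 66 y"), two-sided alpha 0.05, power 80%, allocation 1:1, 34 per group (68 at final assessment), 82 recruited.
- From Section 2.17: one interim look, at 50% of participants having completed T2.
- Not stated: the interim significance level. It is varied below.

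**Step 1. Reproduce the stated sample size.**
n per group = 2 × SD² × (z₀.₉₇₅ + z₀.₈₀)² / difference² = 2 × 19.9² × (1.960 + 0.842)² / 13.6² = 33.6, rounded up to 34. This matches the protocol, so 34 is a single-look figure with no alpha reserved for an interim test. Power at 34 per group is 80.5% by the normal approximation and 79.3% by the t-test.

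**Step 2. Information fraction.**
Counting like with like, 41/82 = 34/68 = 0.5. If 41 T2 completers are set against 68 at the end, the fraction is 41/68 = 0.60.

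**Step 3. Overall type I error with the final test at two-sided 0.05.**
Under the null hypothesis, overall error = 1 − P(|Z₁| < c₁ and |Z₂| < c₂). Here Z₁ and Z₂ are standard normal with correlation √t, t is the information fraction, and c₂ = 1.960. At t = 0.5 the correlation is 0.707.

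| Interim level (two-sided) | Overall error |
|---|---|
| 0.05 | 8.3% |
| 0.0294 | 6.7% |
| 0.01 | 5.5% |
| 0.003 | 5.1% |
| 0.001 | 5.02% |
| 0.0001 | 5.00% (rounded) |

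A simulation of 2 million trials gives 8.3% for the first row. With 0.05 at both looks, the result is 8.6% at t = 0.4 and 8.0% at t = 0.6, so the exact timing matters little.

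**Step 4. A boundary that holds 5%.**
Lan-DeMets O'Brien-Fleming-type spending, applied to 0.025 per side at t = 0.5:
- Alpha spent per side at the interim = 2 × [1 − Φ(2.241/√0.5)] = 0.0015. This gives z = 2.963, two-sided p = 0.003.
- The final critical value is z = 1.969, two-sided p = 0.049.
- Putting c₁ = 2.963 and c₂ = 1.969 into the Step 3 formula gives 0.050.

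Applying the same spending function to the total 0.05 gives 0.0056 and 0.0478, which also holds 5%.

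**Step 5. Cost.**
- Power of the final t-test at 34 per arm is 79.3% at alpha 0.05 and 79.0% at 0.049.
- At the planning effect the expected final z is 13.6 / (19.9 × √(2/34)) = 2.82, so the expected interim z is 2.82 × √0.5 = 1.99.
- The chance of an early stop for SMART is P(Z > 1.960 − 1.99), about 51%, with an interim level of 0.05. With the spending boundary it is P(Z > 2.963 − 1.99), about 17%.

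**The case against.** The strongest reply is that the protocol never says the interim test uses 0.05. It also requires sufficient information, which might be meant as a stricter bar. Numerical boundaries are often left to an analysis plan or a committee charter, and Section 3.3, to which Section 2.17 refers, is not in the text at hand. Section 2.16 gives no level for the final test, so a final 0.05 is inferred from Section 2.10.

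Much of this stands, and it limits the size of the point. A reader might infer that the trial's error rate is 8.3%. The documents do not support that: it is the result only if 0.05 is applied twice, and a strict interim level brings the inflation close to nil. What the reply does not remove is the mismatch within the protocol. A boundary set elsewhere would still need a matching final alpha, and Section 2.10 leaves no room for one.

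Other stronger readings also go too far:
- **An error of 14% to 16%.** This needs success on either TUG or ASCQ to count at both looks. No section says so, and much of that figure is a separate co-primary question.
- **An early-stop estimate about 2.3 times too large.** This assumes a true standardised effect of 0.34, half the planning value of 13.6/19.9 = 0.683. The protocol gives no such figure, and at 0.683 the overstatement is about 1.3- to 1.4-fold.
- **A look at half enrolment.** The trigger is T2 completion, when more than half may already be enrolled.
- **Enrolled participants losing their T3 visit after a stop.** The protocol does not say this. It is silent.

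**Conclusion.** The point holds in conditional form. The protocol commits to a two-directional superiority stop with no boundary, while its alpha and sample size are those of a trial without an interim look. With the final test at 0.05, the overall type I error lies between about 5.0% and 8.3% for interim levels from 0.0001 to 0.05. The top of that range applies if the only level the protocol states is used at both looks. A strict interim level makes the excess negligible but does not bring the total below 5%.

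The figures assume one primary measure, an information fraction of 0.5, approximately normal test statistics, and a final two-sided level of 0.05 taken from Section 2.10. The missing boundary and the single-look sample size depend on none of these. Because the rule decides whether the trial ends, it needs to be settled before interim data are seen.

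**What to change.** 1. In Section 2.17, name the boundary that defines superiority. One suitable choice is Lan-DeMets O'Brien-Fleming-type spending, applied per side, with two-sided p<0.003 at 50% information and p<0.049 at the final analysis. Define sufficient information as the information fraction at which the look takes place, and recompute the boundary if the actual fraction differs.
2. In Section 2.10, state the same final alpha and acknowledge the interim look.
3. Apply the boundary to one named primary measure. The passages on the two-minute walk test, TUG and ASCQ have to be reconciled first. The boundary does not settle which measure that should be.
4. State that participants already enrolled complete T3 and implementation follow-up if recruitment stops early.

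Alternatively, remove the efficacy stop and limit the look to safety and feasibility. No alpha adjustment is then needed.

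The cost is protocol wording and about 0.3 percentage points of power at 34 per arm. The real downside is that an early efficacy stop becomes less likely: about 17% instead of about 51% at the planning effect.
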